#### Data collection

As outcome measures, the trial is assessing the adherence to IMCI guidelines and the correctness of the illness classification, prescription, referral (if necessary) and counselling.

Each selected CSPS is visited for 1 or 2 days at each ‘step’ of the trial by a team of two staff from the evaluation team. One member of staff observes all under-5 children consultations performed by the local health workers while the other reassesses children after their consultation with the local health worker. Our teams notify the head of the health centre the afternoon of the day before our visit.

The first member of the evaluation team records information regarding each consultation in a detailed observation form. Three observation forms were designed, one per age category defined by the IMCI guidelines (i.e. 0–7 days, 7 days–2 months, 2 months–5 years) and pre-tested to include all questions or tasks that a healthcare worker should perform when following the IMCI guidelines. Each observation form is divided into sections corresponding to the different sections in the IMCI protocol for each age category. For instance, the observation form to observe consultations of children from 2 months to 5 years old includes sections for the assessment of danger signs: cough or fast/difficult breathing, diarrhoea, fever, ear problems, anaemia, nutritional status, HIV, immunisation and vitamin A uptake, referral, treatment and counselling. Observations are passive, and the observer never intervenes during the consultation. Information recorded in the observation form also includes whether the nurse referred to the IMCI chart booklet during the consultation or used the REC (if the district benefited from the intervention), as would be expected if IMCI was being implemented correctly. If the health centre has more than one nurse conducting child consultations, the observer follows the first child who is called for consultation.

Following observation of a consultation, the second member of the evaluation team, expert in IMCI, re-assesses the child independently using the REC to provide a ‘gold standard’ against which to compare local health workers’ classifications and treatment decisions. In case of discrepancies between the health worker and the IMCI expert, the final management decision is determined following discussions between the two of them.

In addition to observations and repeat assessments, a questionnaire, based on the WHO Service Availability and Readiness Assessment questionnaire [30], was developed to document the context in which the trial is conducted. This questionnaire is completed at each visit to a CSPS and captures information on the resources available for management of childhood illnesses according to the IMCI guidelines.

Two evaluation teams (each comprised of two members) were recruited for data collection. They had all previously been trained in IMCI by the Ministry of Health and had at least 5 years of experience of IMCI in their health centre. In addition, they underwent 2 weeks of training on the study methods, provided by the investigators.

#### Analysis

The stepped-wedge design can be analysed in different ways [31]. In the primary analysis, each step will be analysed using methods appropriate for a parallel cluster randomised trial, using district-level summaries of the outcome to calculate a difference measure. These difference measures will be combined across steps using inverse variance weighting. Hypothesis testing will be based on bootstrapping or a permutation test.

In the secondary analysis, the method described by Hussey and Hughes [28] will be used. As the outcome is likely to be relatively common, the risk difference will be modelled using generalised estimating equations at the level of the child consultation, with fixed effects for intervention versus control phase, time step and district and clustering at the level of the health centre.

Potential imbalances at the level of the child and the health centre between intervention and control phases will be investigated and any imbalances will be adjusted for. A priori, adjustment will also be made for district-level summaries of the outcome at baseline.

A detailed statistical analysis plan will be prepared before the end of data collection.

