## Background

Despite a large reduction in under-5 child mortality (from 180 per 1000 live births in 1990 to 83 per 1000 live births in 2015), sub-Saharan Africa failed to reach the Millennium Development Goal 4 target of 60 deaths per 1000 live births [1]. In 1999, the World Health Organization (WHO) developed the Integrated Management of Childhood Illness (IMCI) strategy [2]. This strategy provides an algorithm to guide health workers through a systematic clinical assessment of sick children with the aim of improving the diagnostic classification and the treatment of these children [3–5] and hence reducing mortality [4, 6].

However, effective implementation of IMCI is often constrained by poor adherence to the guidelines [7–9]. Previous studies have reported that adherence to the guidelines decreases over time due to inadequate initial training, shortage of staff and insufficient supervision [10, 11]. Takada et al. [12] have noted that healthcare workers typically find the IMCI chart booklet burdensome and try to work from memory, resulting in a decrease in quality of care. In addition, healthcare workers may omit sections resulting in incomplete assessments [4, 13]. Chaudhary [10] demonstrated that the adherence of health workers improved with supervision. However, regular supervision of health workers after training is often lacking [8, 13], partly due to the lack of resources.

Burkina Faso introduced the IMCI strategy in 2003. However, an evaluation conducted in 2013 found that only 22 % of nurses working in primary care facilities had been trained in IMCI [14]. Only 28 % of children were assessed for three danger signs as recommended by IMCI, and only 15 % of children were correctly classified [14]. About 30 % of children were correctly prescribed with an antibiotic for suspected pneumonia or oral rehydration salts (ORS) for diarrhoea, and 40 % were correctly referred [14].

Recent advances in information and communication technologies (ICT) holds the potential to transform healthcare delivery in low-income countries [15–17]. However, no evidence is available on the effect of ICT on adherence to IMCI. Small-scale studies conducted in Tanzania found ICT to be well accepted by healthcare workers during IMCI consultations [7, 16]. However, the experience with using such technology on a large scale is limited.

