### The stepped-wedge trial

Stepped-wedge trials are a type of cluster randomised trial in which clusters receive the intervention at different time points and the order in which they receive the intervention is randomised [23, 24]. Some aspects of the intervention can only be delivered at the district level, and other aspects are most conveniently delivered by district and so, we are using a cluster randomised trial with districts as clusters. The two regions have 11 districts, three of which received the pilot intervention and so, the evaluation will be restricted to the eight remaining districts. The implementing agencies (the MoH and TdH) need to roll out the intervention in a phased implementation approach for logistical reasons, with the intervention introduced into one additional district every 4 months. Hence, we are using a stepped-wedge design, with the order in which the eight districts receive the intervention determined by computer-based, restricted randomisation (Fig. 2).

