**Fig. 2 Fig2:**
[figure not shown]
The sequence of districts receiving the intervention after each period of 4 months during the stepped-wedge trial

The intention was that the intervention would eventually be delivered to all primary health centres in all eight districts. Also, during the period preceding the intervention (i.e. in year 1 step 1), a first round of data collection would be conducted in the eight districts to provide pre-intervention measurements in all districts.

The aim of the trial is to determine whether the IeDA intervention increases adherence to the IMCI algorithm and hence improves classification, referral, prescription and counselling during under-5 child consultations in health centres. This will be determined by observation of child consultations followed by a repeat consultation by study staff in selected CSPS.

There are two co-primary outcomes, one task-based and one results-based, both measured at individual level using direct observation [25–27]:Degree of adherence to IMCI guidelines, measured as a quantitative variableCorrect disease classification and prescription, measured as a binary variable

The secondary outcomes related to under-5 children consultations are as follows:Correct identification of danger signsCorrect classification of childrenPrescription of the correct medicineCorrect referral or hospitalisationCorrect counselling delivered to child carer

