#### Randomisation

There are eight districts (five in Boucle du Mouhoun region and three in the Nord region) in the stepped-wedge trial. Restricted randomisation was used to allocate one cluster (i.e. one district) to receive the intervention in each of the eight time periods [29]. The order in which the eight districts receive the intervention was subject to three constraints that address the following circumstances in which the trial was being performed:An international organisation will be implementing a performance-based financing (PBF) intervention in four of the eight districts during the study, which may influence the performance of the health workers. In addition, two of the eight districts will act as ‘control’ clusters for their study, and so, it would be better if the IeDA intervention does not start in both these clusters before starting in any other cluster.An international donor is prepared to provide support for two of the five districts in the Boucle du Mouhoun region, but they needed to start doing this soon.There needs to be some balance in the randomisation order across the two regions.

Hence, the following restrictions were applied:There must be one PBF intervention district and one PBF non-intervention district (either a control district or one excluded from the study) in each pair of randomised districts, i.e. in the first and second districts to receive the intervention, the third and fourth districts, the fifth and sixth districts and the seventh and eight districts. The difference in the average order of the PBF intervention districts and the non-intervention districts must be less than one. The first three districts must not include both PBF control districts.At least one of the first two districts must be in the Boucle du Mouhoun region.At least one of the first three districts and at least one of the last three districts must be from the Nord region.

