## Discussion

### Interconnected sub-studies

With the IeDA study, we aim for a holistic evaluation in which outcome, process and cost data are integrated in the analysis of the findings to maximise our capacity to understand the effect of the introduction of a complex intervention into a specific context.

In integrating outcome, process and cost data, we focus on three key questions: (i) How does the effectiveness and the cost of the intervention vary by type of health worker and type of health centre? (ii) What is the impact of changes in the content, coverage and quality of the IeDA intervention on adherence and cost-effectiveness? (iii) What mechanisms of change (including costs) might explain the relationship between the IeDA intervention and adherence?

To explore whether more intensive implementation of the IeDA intervention can generate better adherence outcomes, data collected on implementation parameters (e.g. fidelity and dose) will be used to categorise and rank health centres. We will calculate the correlation between outcome and the fidelity and dose of the IeDA intervention.

In addition, process and cost data will be integrated into the trial analysis to identify new hypotheses on factors influencing the performance of health centres. Two factors that may play an important role in performance are (1) the characteristics of health workers (e.g. their experience in IMCI, the time allocated to each consultation) and (2) the characteristics of health centres (e.g. team structure, leadership, resources available).

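### The secondary model's single intervention term recovers the effect only if it is constant over time since roll-out; otherwise long exposures count with negative weight

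*Protocol article*

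**What the plan says.** The Analysis section of the protocol article plans two analyses of the stepped-wedge trial.

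- **Primary.** Districts with and without the intervention are compared within each step on district-level summaries. "These difference measures will be combined across steps using inverse variance weighting".
- **Secondary.** "In the secondary analysis, the method described by Hussey and Hughes [28] will be used", fitted by GEE to the risk difference at consultation level, "with fixed effects for intervention versus control phase, time step and district", with clustering by health centre.

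The secondary model therefore has one intervention term. The article describes no term for time since roll-out.

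Roll-out is staggered "with the intervention introduced into one additional district every 4 months", and the Randomisation section uses restricted randomisation "to allocate one cluster (i.e. one district) to receive the intervention in each of the eight time periods". Before that, "a first round of data collection would be conducted in the eight districts to provide pre-intervention measurements in all districts".

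Two statements bear on whether the effect might change with exposure. The Background says of earlier IMCI studies that "adherence to the guidelines decreases over time due to inadequate initial training, shortage of staff and insufficient supervision". Under Interconnected sub-studies, one of the three key questions is "What is the impact of changes in the content, coverage and quality of the IeDA intervention on adherence and cost-effectiveness".

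**The concern.** The first district to cross over is observed for up to eight steps under the intervention and the last for one. A single term treats all of these as the same effect. Once district and step effects are fitted, districts already treated serve as comparators for districts that cross over later. If the effect changes with exposure, that change is partly absorbed into the step effects and comes out of the estimate with the wrong sign.

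The interpretation of the secondary estimate is at stake. It could be read as the average effect over the trial when it is not one. It could also disagree with the primary estimate for a reason that neither model would reveal. The effect after long exposure, which matters to those who will run the programme, is the part represented worst.

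**Working it through.** **Inputs.** Eight districts, one crossing over per step, and a baseline round (The stepped-wedge trial; Randomisation). Ten centres per district, ten or four children per centre, design effect 2, coefficient of variation 0.3, and 25 % rising to 33 % or 40 % (Sample size calculation). Assumed: nine rounds (baseline plus one after each cross-over), two-sided 5 % level, balanced visits.

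**Step 1: reproduce the stated power.** The Hussey-Hughes variance is

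Iσ²(σ² + Tτ²) / {(IU − W)σ² + (U² + ITU − TW − IV)τ²}

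with I = 8, T = 9, U = 36, W = V = 204, σ² = 0.25 × 0.75 × 2/100 = 0.00375 and τ² = (0.3 × 0.25)² = 0.005625.

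- Numerator: 8 × 0.00375 × 0.054375 = 0.00163125.
- Denominator: 84 × 0.00375 + 420 × 0.005625 = 2.6775.
- SE = √0.000609 = 0.0247, so z = 0.08/0.0247 − 1.96 = 1.28 and power is 0.900 (stated 90 %).

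With four children (σ² = 0.009375) and a 15-point effect, power is 0.978 (stated 98 %). With eight rounds the first figure is 0.874, so nine rounds fits the plan's own numbers.

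**Step 2: weights of the single term.** Let X be the treatment indicator for a district-round. With district and step fixed effects the coefficient is Σ w × effect over treated district-rounds, where

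w = (X − district mean − round mean + overall mean) / D

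and D is the sum of that numerator over the 36 treated cells: D = 36 × 1.5 − 204/9 − 204/8 = 5.833.

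- Exposure step 8 (first district, last round): (1 − 8/9 − 1 + 0.5)/5.833 = −0.067.
- Exposure step 1 (eight cells): (8 × 1.5 − 36/9 − 36/8)/5.833 = 3.5/5.833 = 0.600.

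**Step 3: weights of the primary analysis.** With equal district variance and no covariate adjustment, a step with k treated districts has inverse-variance weight k(8 − k)/8. Summed over k = 1 to 7 this is 10.5. Each treated district in that step then carries (8 − k)/84.

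| Exposure step | Treated cells | Single term | Primary |
|---|---|---|---|
| 1 | 8 | 0.600 | 0.333 |
| 2 | 7 | 0.383 | 0.250 |
| 3 | 6 | 0.207 | 0.179 |
| 4 | 5 | 0.071 | 0.119 |
| 5 | 4 | -0.024 | 0.071 |
| 6 | 3 | -0.079 | 0.036 |
| 7 | 2 | -0.093 | 0.012 |
| 8 | 1 | -0.067 | 0 |

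Both sets of weights sum to 1. The negative part of the single term is -0.26. The primary puts 28/84 + 21/84 + 15/84 = 64/84 = 76 % on steps 1 to 3.

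**Step 4: illustration (assumed effect patterns).** For a linear pattern only the weighted mean exposure matters. It is 0.5 steps for the single term, 2.5 for the primary, 120/36 = 3.33 over treated cells, and 4.5 with equal weight per step. The slope is 8/7 points per step.

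| Summary | Fade, 12 to 4 | Growth, 4 to 12 |
|---|---|---|
| Single term | 12 + 0.5 × 8/7 = 12.6 | 3.4 |
| Primary | 12 − 1.5 × 8/7 = 10.3 | 5.7 |
| True average, treated cells | 12 − 2.33 × 8/7 = 9.3 | 6.7 |
| True average, equal steps | 12 − 3.5 × 8/7 = 8 | 8 |

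A constant effect of 8 points is returned as 8.

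**Step 5: robustness.** With eight rounds the negative weights total -0.17, and a linear trend puts the estimate exactly on the first-step effect (12 or 4). With a random district effect, steps 5 to 8 stay negative (-0.013, -0.065, -0.081, -0.059). Simulated identity-link GEE fits clustered by health centre, with independence or exchangeable correlation and equal or unequal visit sizes, gave estimates close to those the weights predict. The planned adjustment for baseline district outcome is constant within a district, so the district effects absorb it.

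**The case against.** Several objections have force.

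- **It is the secondary model.** The primary analysis, which carries the main conclusion, has no negative weights. This stands.
- **A changing effect is not shown.** A reader might infer from the Background that IeDA's effect will fade, or from the Discussion that the intervention will change. The documents do not support either inference. The first statement concerns IMCI in general and blames weak training and supervision, which IeDA's training course and monthly supervision address. The second is a research question. Both make a changing effect plausible and no more.
- **The benchmark matters.** Against the equal-step average of 8, the single term is 4.6 points out. Against treated district-rounds it is 12.6 − 9.3, about 3.2 before rounding. The overshoot beyond every true effect is only 0.6 points here, and some patterns stay inside the range: 4, 6, then 8 points gives 4.8 against an equal-step average of 7.25.
- **Cost-effectiveness.** A reader might infer that the cost-effectiveness ratio inherits the error. The Cost-effectiveness analysis section does not say which effect estimate it uses, so that does not follow.
- **The analysis plan is still to come.** An exposure-time sensitivity analysis may well be placed there, and its absence from an article is no fault. The single term, however, is stated in the article, and the weights follow from it.
- **Precision.** Replacing the single term outright would be a trade of bias against variance, not the correction of an error. This stands, and it shapes the fix.

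**Conclusion.** The point holds as a limited one. As written, the secondary model estimates the treatment effect only under a constant effect over time since roll-out. Otherwise its estimate is dominated by early exposure (weights of 0.60 + 0.38 + 0.21 = 1.19 on the first three steps) and counts exposures of five steps or more negatively. In the assumed linear examples it misses the average over treated district-rounds by about 3.2 points either way, beside a design difference of 8 points. The primary estimate misses by about 1.0.

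The weights rest on nine rounds, which the article does not state but its power figures support, and on balanced visits. The sizes rest on invented effect patterns. Exposure is counted in steps because the article does not say when a visit falls after roll-out. Nothing here shows that the primary conclusion would be wrong. This is a cheap improvement, not a flaw that invalidates the plan.

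**What to change.** Keep the single-term model as planned. In the statistical analysis plan, which the article says will be prepared before data collection ends:

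1. Pre-specify a sensitivity analysis that replaces the single term by exposure-step indicators, preferably grouped as 1-2, 3-4 and 5 or more steps. Report the group effects and their average, with the averaging weights stated.
2. State that the primary and single-term estimates mainly reflect the first three exposure steps.

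The data needed are already planned. With nine rounds even eight separate indicators can be estimated (24 parameters, full rank). The cost is precision. Under the plan's variance inputs with district and step fixed effects, the single term has SE √(0.00375/5.833) = 2.5 points. The equal-step average has SE 4.2 points with eight indicators. With the three groups it is 3.7 if groups are weighted by number of steps, 3.4 if weighted equally, and 3.2 if weighted by treated district-rounds. That loss is the reason to add this analysis beside the planned model and not in its place.

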### Selection of primary health centres

The evaluation is being conducted in ten randomly chosen primary health centres per health district. The list of CSPSs selected for the evaluation has not been communicated to the implementing agency to reduce the likelihood that they target these health centres for more intensive support. Ten CSPS per district was chosen to give sufficient contextual variation, while minimising logistical difficulties and ensuring that some CSPS in each district were not selected to allow for selection concealment. Only primary health centres with staff trained in IMCI were considered for selection, and all hospitals were excluded. The intervention effect may vary by health centre workload, and so, the selection was stratified on the 2013 annual under-5 consultations caseload, as provided by the MoH. For the 337 CSPSs with staff trained in IMCI in the eight districts under evaluation, the annual caseload was transformed into a daily rate by dividing it by 261 days (i.e. the number of working days). Out of the 337 CSPSs, 13 were excluded, either because of missing caseload data (six CSPS) or because of a zero recorded caseload (seven CSPS). Out of the remaining 324 CSPSs, a further 54 CSPSs were excluded because they had caseloads of less than three cases per working day, which would have limited the number of consultations that could be observed in these facilities. Although these 54 CSPSs represented 17 % of the remaining 324 CSPSs, they only represent 4 % of the total caseload in 2013. In each district, five CSPSs were then randomly selected among those with fewer than seven cases per working day and five CSPSs were randomly selected among those with seven cases or more per working day (on average). Seven cases were chosen for the cutoff as this ensured there were at least nine CSPSs in each of the two strata in each district. Data will be collected in the same ten CSPSs per district during each step of the stepped-wedge trial during a 1- to 2-day visit (see the ‘Data collection’ section below).

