#### Sample size calculation

Using the method described by Hussey and Hughes [28] and assuming that:Ten health centres in eight districts will be visited every step.A harmonic mean of ten children will present at each health facility over the course of a 1- to 2-day visit.Sampling ten children per facility per round carries a design effect of 2.The coefficient of variation between clusters is 0.3.

Then, there is 90 % power to detect an increase in the correct diagnosis and treatment from 25 to 33 %. If there is only a harmonic mean of four children at each health centre, there will be 98 % power to show an increase from 25 to 40 %.

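### The secondary GEE takes its standard error from health centres although districts are randomised, so its type I error can exceed 5 % if districts vary from step to step

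*Protocol article*

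**What the plan says.** The section on the stepped-wedge trial gives the unit of allocation: "we are using a cluster randomised trial with districts as clusters". The Randomisation section repeats it: "Restricted randomisation was used to allocate one cluster (i.e. one district) to receive the intervention in each of the eight time periods". Each district contributes ten health centres, revisited throughout: "Data will be collected in the same ten CSPSs per district during each step of the stepped-wedge trial".

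The Analysis section plans two analyses:

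- **Primary.** District-level summaries are compared within each step and combined across steps by inverse variance. Testing is by bootstrap or permutation.
- **Secondary.** The Hussey and Hughes approach is fitted to individual consultations as a GEE for the risk difference. The model is specified as one "with fixed effects for intervention versus control phase, time step and district and clustering at the level of the health centre".

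The sentence on bootstrap or permutation testing belongs to the primary analysis, and nothing shown extends it to the GEE. The article promises a detailed SAP, but the clustering level is already chosen here, so the SAP would have to reverse a choice rather than fill a gap.

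**The concern.** The fixed effects in the GEE cover two kinds of variation: differences between districts that never change, and changes over time that are common to all districts. They do not cover a change that affects one district in some steps and not others. The ten centres of that district share such a change. A sandwich variance clustered on centres allows for correlation between repeated visits to one centre, but takes different centres as independent given the fixed effects.

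The treatment contrast is also set at district-by-step level, so a shared shock feeds straight into the estimated effect. The centre-level sandwich sees only about one tenth of the variance it causes. Confidence intervals are then too narrow and p-values too small. A significant secondary result could stand beside a non-significant primary one for this reason alone.

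**Working it through.** **Inputs from the protocol article**

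- Eight districts, one crossing over per period, plus a baseline round ("a first round of data collection would be conducted in the eight districts to provide pre-intervention measurements in all districts"): I = 8 districts and T = 9 rounds.
- Ten centres per district; "A harmonic mean of ten children will present at each health facility over the course of a 1- to 2-day visit"; "Sampling ten children per facility per round carries a design effect of 2".
- Coefficient of variation between clusters 0.3 at 25 %: district SD 0.3 × 0.25 = 0.075, variance τ² = 0.005625.
- Variance of a district-by-step mean: σ² = 0.25 × 0.75 × 2 / (10 × 10) = 0.00375.

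**Assumptions:** two-sided 5 % level; s, the share of τ² that is specific to the step.

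**1. The plan's own power.** With X the treatment indicator, U = ΣX = 36, W = Σ(step totals)² = 204 and V = Σ(district totals)² = 204. The Hussey and Hughes variance is

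Iσ²(σ² + Tτ²) / [(IU − W)σ² + (U² + ITU − TW − IV)τ²]

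= 8 × 0.00375 × 0.054375 / (84 × 0.00375 + 420 × 0.005625)

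= 0.00163125 / 2.6775 = 0.000609, so SE = 0.0247.

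Then 0.08 / 0.0247 − 1.96 = 1.28, which gives 90.0 % power (stated: 90 %). With four children per centre, σ² = 0.009375 and SE = 0.0378, which gives 97.8 % for 25 to 40 % (stated: 98 %). The inputs are therefore read as the plan intends. This formula has no district-by-step term, so it corresponds to s = 0.

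**2. True against reported variance of the GEE estimate.** With district and step fixed effects, the information on the treatment effect is

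D = U − W/I − V/T + U²/(IT) = 36 − 25.5 − 22.667 + 18 = 5.833.

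- True variance: (σ² + sτ²) / D.
- Variance seen by the centre-level sandwich, approximately: (σ² + sτ²/10) / D.

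At s = 0.2:

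- true SE = √(0.004875 / 5.833) = 0.0289;
- reported SE = √(0.0038625 / 5.833) = 0.0257;
- ratio 1.123, so the actual two-sided error is 2 × [1 − Φ(1.96 / 1.123)] = 8.1 %.

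**3. Simulation under no effect.** The table sets this formula beside repeated simulations (80 centres, nine rounds, same inputs).

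| Share s | District-by-step SD | Formula | Simulated type I error |
|---|---|---|---|
| 0 | 0 | 5.0 % | 5.7 to 6.3 % |
| 10 % | 2.4 points | 6.6 % | 6.3 to 7.7 % |
| 20 % | 3.4 points | 8.1 % | 7.8 to 9.4 % |
| 40 % | 4.7 points | 11.1 % | 11.4 to 12.0 % |
| 50 % | 5.3 points | 12.4 % | 12.9 to 13.8 % |

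The simulated mean reported SE is about 0.025 against a true 0.029 at 20 %, and 0.026 against 0.034 at 50 %.

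**4. Sensitivity.** A separate simulation used binary outcomes at a base rate of 29 %. It gave 5.0 to 5.6 % at a district-by-step SD of zero, 8 to 9 % at 3 points and 13 to 14 % at 5 points. At 5 points, eight rounds gave 13.7 %, a step-to-step correlation of 0.7 gave 13.2 %, and four children per centre gave 10 %.

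**5. Candidate remedies on simulated data.**

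- Permuting district order gave 3.8 to 5.2 % with unrestricted permutations, and about 4 to 5 % over the 4224 acceptable allocations.
- A sandwich on the eight districts gave about 11 to 12 % with normal critical values, and about 6 to 7 % with t on 7 degrees of freedom.

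**The case against.** **The inflation is conditional.** The article gives one coefficient of variation and no step-specific part. At zero, the model is close to nominal. A reader might infer that the false-positive rate exceeds 5 % whatever happens; the document does not support that. This objection stands, and every materially inflated figure above depends on the assumed share.

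**It is a secondary analysis.** The primary analysis works on district summaries and respects the randomised unit, and nothing lets the GEE override it. This stands. Nor does the GEE carry the trial's stated power: the sample-size section uses the Hussey and Hughes formula with between-district variation, not a health-centre sandwich.

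**Performance-based financing is a poor example.** The Randomisation section says a financing programme will run as an "intervention in four of the eight districts during the study, which may influence the performance of the health workers", and a reader might take this as the source of a 7 to 14 % error. The restrictions largely balance it. Placing two financed districts and one excluded district in the Nord region reproduces the published counts of 4224, 292 and 720. Over those allocations, a common shift in all four financed districts, starting together at any step, moves the estimate by at most 0.17 of its size (SD at most 0.09). A 5-point shift therefore moves it by at most 0.17 × 5 ≈ 0.9 points, against a standard error of about 2.5 points. Uneven or staggered effects could do more, but the document does not describe them.

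**The model does not treat the data as 80 unrelated units.** District effects remove permanent differences, and the sandwich covers repeat visits. Only district-by-step changes are missed.

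**Covariates may absorb some of it.** Resources are recorded at each visit, and adjustment for imbalances is planned. This helps only in part, because it reaches only what is measured.

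What remains is the mechanism. District teams supervise the centres, training is delivered by district, and each district is encouraged to find its own solutions. A district-by-step variance of exactly zero is therefore a strong assumption for the standard error to rest on.

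**Conclusion.** The point holds in conditional form, as something to fix rather than a fatal flaw. The secondary GEE's standard error is too small whenever districts vary from step to step beyond the common time trend. Under the plan's inputs the type I error is then about 6 to 8 % at a 10 % step-specific share, 8 to 9 % at 20 % and 13 to 14 % at 50 %, against about 6 % at zero. The direction is certain if such variation exists; the size rests on a share the document does not give. The primary analysis and the trial's main conclusion are untouched.

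**What to change.** Keep the GEE and its point estimate, and change the basis of inference:

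- **Preferred.** Obtain the p-value by recomputing the estimate under each of the 4224 acceptable allocations of district order, and the confidence interval by inverting that test. This matches how the order was drawn and uses a set that already exists.
- **Alternative.** Use a district-level robust variance, or a model with a district-by-step random effect, in either case with a small-sample correction for eight districts. A plain sandwich on eight districts with normal critical values is not enough, as the 11 to 12 % above shows.

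The SAP should state the choice before the end of data collection. If the health-centre interval is still reported, label it as assuming no district-by-step variation. The cost is SAP wording, some programming and somewhat wider intervals; no new data are needed.
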